#### Investigator

The principal investigator ([name]) will also be an external evaluator. Though, an Alarm Distress Baby Scale–trained psychologist, [name] will not participate in the follow-up of any of the infants and will be blind to the Alarm Distress Baby Scale scores of the Alarm Distress Baby Scale–trained neonatologists. Scores will be entered into the database by an independent agent who is blind to the group category.

#### Outcome Assessment

The Alarm Distress Baby Scale–trained neonatologists will be blind to the Alarm Distress Baby Scale scores of the external evaluators and to those of the other Alarm Distress Baby Scale–trained neonatologists. Once they record an Alarm Distress Baby Scale score, this data will be collected by a study coordinator, who is blind to the group category.

#### Data Collection Assessors

Data collection assessors will collect all study data (all variables) and upload the data into the database. They were not trained in the Alarm Distress Baby Scale, are blind to the group category, and do not have contact with the infants or their families.

### Sample Size

We used the G*Power 3 software (Psychonomic Society Inc) to determine the minimum sample size required for obtaining a significant medium effect size (an effect size of 0.25), given α=.05 and a statistical power of 0.80 (β=.20), using the results presented in Bonifacino et al [37]. In Bonifacino et al’s study [37], the dependent variable was assessed in 4 different stages, with 3 of them involving the total sample. Also, between the second and third assessments, the control group received the intervention. Because of this, we considered the observed differences between the first and second assessments in order to compute our sample size (postintervention difference in prevalence of 57% for the control group and 13% for the intervention group). The resulting sample size estimate was 23 per group; however, in order to ensure a sufficient effect size and taking attrition into consideration, a sample size of 55 infants per group will be used.

### Assessment Instruments

Alarm Distress Baby Scale [9] reliably (Cronbach α=.83) assesses sustained social withdrawal behavior in infants from 2 to 24 months of corrected age during routine physical examination. It consists of 8 items (lack of facial expression, eye contact, general movement, self-stimulation gestures, vocalization, liveliness in response to any stimulation, ability to establish and maintain a relationship, and ability to attract and catch the attention of others) each scored from 0 (normal behavior) to 4 (massively abnormal behavior). A total score of 5 or more indicates sustained social withdrawal behavior. The assessment can be done during routine pediatric checkup by a trained professional, or by assessment of an 8 to 12-minute video of recorded infant behavior during a pediatric checkup.

Edinburgh Postnatal Depression Scale [45] reliably (Cronbach α=.77) assesses the probability of postnatal depression in women. It consists of 10 questions with 4 possible answers for each. Each answer is given a score of 0, 1, 2, or 3 according to the severity of the symptom. The maximum score is 30. A total score of 12 or higher suggests the presence of a postnatal depression disorder. The Edinburgh Postnatal Depression Scale can be administered from 2 months onward, after delivery.

Impact of Event Scale–revised [46] reliably (Cronbach α=.98) assesses symptoms associated with posttraumatic stress disorder. It is composed of 22 items and three subscales: intrusion, avoidance, and hyperactivation. It employs a 5-point Likert scale from 0 (not at all) to 4 (extremely), to assess the intensity of the symptoms. The Impact of Event Scale–revised can be applied from six weeks onward, after the occurrence of a stressful or traumatic event. Scores higher than 24 indicate significant clinical relevance.

Modified Perinatal Posttraumatic Stress Disorder Questionnaire [47] reliably (Cronbach α=.90) assesses posttraumatic stress symptoms in parents including intrusiveness or reexperiencing, avoidance behaviors and hyperarousal, or numbing of responsiveness. It consists of 14 items, which are measured using a 5-point Likert scale from 0 to 4. Parents are instructed to provide responses that reflect their experience during the 4th and 18th month after delivery. The total score can range from 0 to 56. The clinical range for a high-risk parent is set at 19 or higher.

Premature Infant Pain Profile [48] is a reliable (Cohen κ≥0.85, consistently) 7-indicator composite measure developed to assess acute pain in preterm and term neonates . The 7 indicators are gestational age, behavioral state, heart rate, oxygen saturation, brow bulge, eye squeeze, and nasolabial furrow. Each indicator is numerically scored using a 4-point Likert scale from 0 to 4, and total scores can range from 0 to 21. Higher total scores indicate greater pain. Premature Infant Pain Profile scores below 6 means no pain, 6 or higher indicates pain, and 12 or higher indicates moderate to severe pain.

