## Methods

### Study Design

The study is designed as a randomized controlled trial (NCT03212547), in order to remove bias in treatment allocation and the effect of possible confounding variables [41]. Chilean infants who were born moderately preterm or late preterm (up to N=110) and their parents will be included and randomized in a 1:1 allocation ratio to an intervention group (up to n=55) and a control group (up to n=55). Both groups will receive routine pediatric care at medical checkups at 2, 6, and 12 months of age. All ages used in this study refer to corrected age. To calculate corrected age, the difference in weeks of gestation at the time of birth and full term (40 weeks of gestation) is subtracted from the infant’s chronological age. In addition, the intervention group will receive the interactive guidance intervention, performed by Alarm Distress Baby Scale–trained neonatologists, if the neonatologists detect sustained social withdrawal (a score of 5 or higher in the Alarm Distress Baby Scale) during the routine medical checkups. The interactive guidance intervention will follow a standardized protocol designed by the research team before the start of the recruitment. The control group will not receive the interactive guidance intervention during the first 12 months; however, if any infant in the study receives a score of 5 or higher on the Alarm Distress Baby Scale at the 12-month checkup, they will be offered further assessment and intervention.

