### Inclusion Criteria

Only preterm infants born from single or twin pregnancy (monochorionic or dichorionic), born between 32 weeks 0 days and 36 weeks 6 days gestation (as determined by neonatologist), hospitalized within the first 48 hours after birth, and remaining at least 48 hours in the neonatal intensive care unit were eligible to participate in this study. Parents of the infants were required to be Spanish speaking and have stable living arrangements to ensure the effectiveness of the interactive guidance intervention (carried out by Spanish-speaking neonatologists). Parents of infants born preterm were recruited from two neonatal intensive care units—Clinica Alemana de Santiago and Hospital San Jose—by a principal investigator or co-investigator of the study or by the neonatal study coordinator. Clinica Alemana de Santiago is a private health center located in a district of Santiago, Chile with a poverty rate of 0.1% whereas Hospital San Jose is a public health center located in a district of Santiago, Chile with a poverty rate of 8.2% [42,43]. At enrollment, socioeconomic variables were recorded using a socioeconomic survey, and pregnancy and postpartum variables were recorded using a perinatal background questionnaire.

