As shown in Figure 1, all infants will receive routine pediatric care during the medical checkups at 2, 6, and 12 months of age, but in addition, infants in the intervention group will also receive the interactive guidance intervention if the Alarm Distress Baby Scale–trained neonatologists detect sustained social withdrawal during these medical checkups. All medical checkups will be video-recorded, and the videos will be assessed by external Alarm Distress Baby Scale–trained evaluators, and at every medical checkup, parents will fill out the Edinburgh Postnatal Depression Scale, the modified Perinatal Posttraumatic Stress Disorder Questionnaire, and the Impact of Event Scale–revised.

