#### Secondary Outcome Measures

The secondary outcomes measured during neonatal intensive care unit admission are neonatal pain and daily duration of parental visits, skin-to-skin contact, and breastfeeding; and the secondary outcomes measured after medical discharge are postpartum depression symptoms and posttraumatic stress symptoms which will be assessed at the 2, 6, and 12-month medical checkups. A socioeconomic survey, a substance-use survey, and a perinatal background questionnaire will be used to obtain additional information from the parents of the infants.

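### The modified Perinatal PTSD Questionnaire is scheduled at the 2-month corrected visit, which falls before, or at most under four weeks into, the period its stated instruction asks parents about

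*Protocol article*

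**What the plan says.** Under Assessment Instruments, the protocol article describes the modified Perinatal Posttraumatic Stress Disorder Questionnaire as 14 items scored 0 to 4, with a total of 0 to 56 and a high-risk range from 19 upward. On timing it states: "Parents are instructed to provide responses that reflect their experience during the 4th and 18th month after delivery".

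The Protocol section schedules it without exception: "at every medical checkup, parents will fill out the Edinburgh Postnatal Depression Scale, the modified Perinatal Posttraumatic Stress Disorder Questionnaire", together with the Impact of Event Scale–revised. Secondary Outcome Measures confirms the times: "postpartum depression symptoms and posttraumatic stress symptoms which will be assessed at the 2, 6, and 12-month medical checkups".

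These visit times are corrected ages. Study Design says "All ages used in this study refer to corrected age" and gives the conversion: "the difference in weeks of gestation at the time of birth and full term (40 weeks of gestation) is subtracted from the infant’s chronological age". Inclusion Criteria limits gestation to infants "born between 32 weeks 0 days and 36 weeks 6 days gestation".

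For the other two parent scales, Assessment Instruments gives an earliest time of use. The Edinburgh Postnatal Depression Scale has a start of 2 months after delivery. The Impact of Event Scale–revised "can be applied from six weeks onward, after the occurrence of a stressful or traumatic event".

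**The concern.** The questionnaire's reference period is counted from delivery and begins at month 4, but its first administration is at 2 months corrected age. Preterm infants are older chronologically than their corrected age, so the conversion might have closed the gap. The question is whether it does.

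If it does not, a parent who follows the stated instruction at the first visit must answer about time that lies wholly or almost wholly ahead, or must set the instruction aside. Either way, the 2-month score refers to a different period from the scores at 6 and 12 months. A change from 2 to 6 months, or a covariate that pools the visits, would then mix two quantities. One high-risk cut-off of 19 is given with no distinction between visits.

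Posttraumatic stress symptoms are a secondary outcome. Posttraumatic stress is also listed among the covariates under Statistical Analysis, and its relation to sustained social withdrawal is part of the objective stated in the abstract.

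**Working it through.** The article states no figure for chronological age at the visits, so there is none to reproduce. The check is date arithmetic on its own definitions.

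**Inputs**
- Term is 40 weeks = 280 days (Study Design).
- Gestation at birth is 32w0d = 224 days to 36w6d = 258 days (Inclusion Criteria).
- Visits are at 2, 6 and 12 months corrected age (Study Design; Secondary Outcome Measures).
- Assumptions: one month = 365.25/12 = 30.44 days, and each visit takes place at exactly its nominal age. The article gives no visit window.

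**Formula.** Corrected age is chronological age minus (280 − gestation in days). Hence chronological age = corrected age + (280 − gestation in days).

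**First visit.** Two months is 60.9 days, three months 91.3 days and four months 121.75 days.

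| Gestation | Correction (days) | Days after delivery | Months after delivery | Short of 4 months (days) | Past 3 months (days) |
|---|---|---|---|---|---|
| 32w0d | 56 | 116.9 | 3.84 | 4.9 | 25.6 |
| 34w0d | 42 | 102.9 | 3.38 | 18.9 | 11.6 |
| 35w4d | 31 | 91.9 | 3.02 | 29.9 | 0.6 |
| 35w5d | 30 | 90.9 | 2.99 | 30.9 | −0.4 |
| 36w6d | 22 | 82.9 | 2.72 | 38.9 | −8.4 |

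**Later visits**
- 6 months corrected: 204.6 to 238.6 days, or 6.72 to 7.84 months after delivery.
- 12 months corrected: 387.2 to 421.2 days, or 12.72 to 13.84 months after delivery.

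**Three readings of the reference period**
1. *A span opening at 4 completed months.* Every infant seen at the nominal first visit is too young, by 5 to 39 days. The two later visits lie inside the span.
2. *A span opening when the fourth month begins, at 3.0 months.* Infants born at 35w5d to 36w6d are wholly before it. Those born at 32w0d to 35w4d are 0.6 to 25.6 days into a period of about 15 months (3.0 to 18.0). The later visits lie inside.
3. *Two separate single months, the fourth and the eighteenth.* The 6- and 12-month visits fall in neither, so the mismatch is wider.

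No reading brings all three visits inside the stated period.

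**Sensitivity.** With 4-week months, a 32w0d infant is at (56 + 56)/28 = 4.0 months at the first visit, which is the boundary itself. A visit 5 or more days late also takes that infant past 4 calendar months. For a 36w6d infant, the delay would have to be 39 days.

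**The other scales.** At 82.9 days or more after delivery, the first visit meets the 2-month start of the depression scale. It also meets the six-week (42-day) start of the Impact of Event Scale–revised, if the stressful event is dated to the birth.

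**The case against.** The strongest reply has four parts.

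*The wording is loose.* The article joins the 4th and the 18th month with the word and, not to. The sentence may be an imperfect paraphrase of a source that is not at hand. This stands to the extent that the span is an interpretation. It does not rescue the schedule, because the literal alternative fits the visits even less well.

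*The fourth month may already have begun.* A reader might infer that the first assessment asks every parent about a period that has not happened at all. The documents do not support that. On the ordinal reading, infants born at 32w0d to 35w4d have entered the fourth month, and late visits would move some past 4 completed months. What remains is that those families are under four weeks into the period, and the later births have not entered it.

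*The article does not call early scores invalid.* This is correct. It describes what parents are asked to reflect on, gives no earliest time of use for this scale, and may leave an adapted form to the full protocol. Outside the stated reference period is as far as the text goes. But the article states both the instruction and the schedule, and nothing in it reconciles them.

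*The analytic reach is limited.* Statistical Analysis names posttraumatic stress as a covariate without saying which scale or visit. Its comparison between times concerns sustained social withdrawal, so no longitudinal model of this questionnaire is specified. The cut-off of 19 is given as a property of the instrument, not as an endpoint. The Impact of Event Scale–revised measures symptoms of the same disorder at the same visit. All of this stands: the effect on the covariate is possible, not established.

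**Conclusion.** The conflict between Assessment Instruments and the visit schedule is real, and conversion to chronological age does not remove it. At the nominal 2-month corrected visit, 2.72 to 3.84 months after delivery, no infant has reached 4 completed months. On the more generous reading, births at 35w5d to 36w6d are wholly before the period and the others at most about 26 days into it. The 2-month scores therefore do not share the reference period of the 6- and 12-month scores.

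This concerns one of the three planned administrations of one of two posttraumatic stress scales. It touches a secondary outcome directly and the posttraumatic stress covariate possibly. A reader might infer damage to the primary outcome, but the Alarm Distress Baby Scale score does not depend on this questionnaire. Nor should the size be put at 110 infants: parents complete the form, and twins are eligible, so families may number fewer than 110.

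The conclusion rests on reading the stated months as a span, on visits at the nominal age, and on calendar months. It also assumes that the instruction as printed is the one given at the first visit. The point is worth correcting because the correction is cheap.

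**What to change.** Reconcile Assessment Instruments with the Protocol and Secondary Outcome Measures sections by stating the recall period actually given to parents at each of the three visits.

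If the first-visit form used a different recall period, say so, and do not treat its scores as interchangeable with the later ones without justification.

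If the 4-to-18-month period stands:
- use this questionnaire and its 19-point classification as an outcome or covariate at 6 and 12 months only;
- report its 2-month scores as exploratory;
- name the Impact of Event Scale–revised as the posttraumatic stress measure at 2 months.

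The cost is wording in the analysis plan and one fewer time point for this questionnaire. No new data are needed. Enrolment was complete by May 2020, so the remedy lies in the analysis, and the replacement measure is already collected at that visit.

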### Intervention

As shown in Figure 2, this interactive guidance intervention consists of a brief, nonintrusive, behaviorally focused intervention performed during medical checkup and which follows a simple protocol that is based on the intervention proposed by Bonifacino et al [38].

**Figure 2 figure2:**
[figure not shown]
Summary of the steps of the interactive guidance intervention during medical checkup.

The main objective of this intervention is to reduce sustained social withdrawal behaviors in moderately and late preterm infants by (1) detecting sustained social withdrawal behaviors during medical checkup, (2) becoming attuned with the interaction rhythm of the infant, (3) meaningfully showing parents how their infant seeks to interact by pointing out specific interactive behaviors (every interaction skill displayed by the infant), and ( 4) inviting parents to engage in the interaction.

Infants born preterm have a higher probability of developing sustained social withdrawal, and withdrawn infants show poor performance during interaction [17,49]; therefore, by facilitating parental understanding of the development of their infant, by involving them in the observation of and interaction with their infant [50], and by reinforcing every seeking interactive behavior displayed by the infant during medical checkups, we can reduce sustained social withdrawal in these infants.

In the intervention group, this interactive guidance intervention will be performed if the trained neonatologist detects sustained social withdrawal during the 2, 6, and 12-month medical checkups. The interactive guidance intervention will be performed during the 20 to 30-minute medical checkup and will not require any extra time. The interactive guidance intervention will be supplemented with a written guide for parents called Early Interaction Guidelines. The objective of this written guideline is to enhance the effect of interactive guidance intervention.

In the control group, infants will receive routine pediatric care. At the 2, 6, and 12-month medical checkups (also lasting 20 to 30 minutes), parents will be given a Development Stimulation Guide which has been adapted from Ministry of Health of Chile Guidelines for the Stimulation of Development [51,52].

If any infant in the study (in either the intervention or the control group) shows sustained social withdrawal (a score or 5 or higher on the Alarm Distress Baby Scale) at the 12-month medical checkup, they will be offered additional interventions by the researcher team.

### Outcomes

#### Primary Outcome Measure

The primary outcome is sustained social withdrawal assessed using the Alarm Distress Baby Scale. The Alarm Distress Baby Scale categorizes the level of sustained social withdrawal according to the sum of the score—scores from 0 to 4 indicate no sustained social withdrawal, scores from 5 to 9 indicate moderate sustained social withdrawal, and scores equal to or higher than 10 indicate severe sustained social withdrawal. Infants born moderately or late preterm will be assessed with the Alarm Distress Baby Scale during medical checkups at 2, 6, and 12 months of age.

#### Secondary Outcome Measures

The secondary outcomes measured during neonatal intensive care unit admission are neonatal pain and daily duration of parental visits, skin-to-skin contact, and breastfeeding; and the secondary outcomes measured after medical discharge are postpartum depression symptoms and posttraumatic stress symptoms which will be assessed at the 2, 6, and 12-month medical checkups. A socioeconomic survey, a substance-use survey, and a perinatal background questionnaire will be used to obtain additional information from the parents of the infants.

### Statistical Analysis

Two-tailed paired *t* tests will be used to compare covariates and dependent variables from the infant groups. A one-way analysis of covariance will be used to determine the effects of covariates (sociodemographic and neonatal intensive care unit hospitalization variables, postpartum depression, and posttraumatic stress) on the comparisons between groups (control and intervention) and between times (2, 6, and 12 months of corrected age medical checkups) regarding the dependent variable (sustained social withdrawal). Other statistical techniques such as matching, odds ratios, and logistic regression will also be used.

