### Protocol

For this study, in 2017, Bonifacino et al [38] conducted Alarm Distress Baby Scale training in Chile over 4 days which consisted of 30 hours and 12 training modules. The program featured 2 central theoretical modules which covered early interactions and emotional development, emotional deprivation and its consequences, social withdrawal behaviors as an early alarm sign, and the Alarm Distress Baby Scale fundamentals. Subsequently, 10 modules of video training were presented featuring material with infants between 2 and 24 months of age. These infants had attended medical checkups with Alarm Distress Baby Scale–trained and untrained pediatricians. Following the videos, there was an exam to certify the professionals in the use of the Alarm Distress Baby Scale. Fleiss kappa was used to determine if there was agreement between the 11 evaluators regarding diagnosis (normal behavior or sustained social withdrawal). There was a substantial agreement [44] between evaluators (κ=0.794, 95% CI 0.676-0.913; *P*˂.001). Individual kappa values for normal and sustained social withdrawal categories were κ=0.795 and κ=0.794, respectively.

One fundamental element of the training was that the professionals learned not only to detect the sustained social withdrawal behaviors (and to score these behaviors using the Alarm Distress Baby Scale), but also to meaningfully show the parents how—in terms of communication or contact—their infants seek interaction, with the objective of reducing sustained social withdrawal behaviors.

Participants of the study will be recruited during their admission to the neonatal intensive care units by members of the researcher team and enrolled and randomized by a study coordinator to either the intervention or the control group. The infant will be randomized in a 1:1 allocation using SPSS Statistics (version 25.0; IBM Corp), stratified by hospital center (Clinica Alemana de Santiago or Hospital San Jose) in blocks of four. Also, infants will be stratified into two groups, single or twin pregnancy, in order to isolate the intervention effect from that of other covariables (such as mother of twins learning). The Hospital San Jose sample will also be stratified into two groups, whether the infant is included or is not included in the Kangaroo Care program, since only Hospital San Jose currently offers this program that aims to promote mother infant bonding, and which could potentially act as a confounding variable.

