#### Care Providers

Neonatologists who care for participants during the trial will be aware of whether the infant is in the intervention or control group. The Alarm Distress Baby Scale–trained neonatologists will only perform follow-up for the intervention group, and neonatologists who provide routine pediatric care will only perform follow-up for the control group.

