### Study Limitations

One of the limitations of this study is the possibility that the parents of infants included in the intervention group will share information with parents of infants included in the control group. For this reason, twins are randomized together (both either in the control or in the intervention group). Additionally, all parents included in the study will be asked to refrain from sharing the written guides used in the study with others until the study is finished.

Another limitation is the pain protocol established at each institution. Clinica Alemana de Santiago has had a standardized pain protocol since 2012 that includes administering the Premature Infant Pain Profile every 3 hours while, in Hospital San Jose, the standardized pain protocol does not include the Premature Infant Pain Profile. Before the start of study recruitment, training was performed by nurses of Clinica Alemana de Santiago in order to teach the midwives in Hospital San Jose how to administer the Premature Infant Pain Profile. At Hospital San Jose, this is only done for the infants included in the study.

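### Paired t tests are named for comparing two independently randomised arms, and the article defines no pairing between an intervention infant and a control infant

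*Protocol article*

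**What the plan says.** The Statistical Analysis section opens with the sentence "Two-tailed paired *t* tests will be used to compare covariates and dependent variables from the infant groups". The next sentence identifies the groups as control and intervention. It gives the effect of covariates on the group and time comparisons to a one-way analysis of covariance. The section closes with "Other statistical techniques such as matching, odds ratios, and logistic regression will also be used". None of these analyses is called primary.

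The rest of the article describes independent parallel arms:

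- Study Design: infants are "randomized in a 1:1 allocation ratio to an intervention group (up to n=55) and a control group (up to n=55").
- Protocol subsection of Methods: allocation is "stratified by hospital center (Clinica Alemana de Santiago or Hospital San Jose) in blocks of four", with further strata for single or twin pregnancy and, at the public hospital, for Kangaroo Care.
- Blinding, Care Providers: each arm has its own clinicians; "neonatologists who provide routine pediatric care will only perform follow-up for the control group".
- Study Limitations: "twins are randomized together (both either in the control or in the intervention group").

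**The concern.** A paired t test works on differences within pairs, so every observation in one arm must have an identified partner in the other. This design supplies no such partners. Blocks of four balance the allocation but do not link individual infants. Twins are the only natural pairs, and they always fall in the same arm.

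Whoever runs the test as written must choose a pairing, for example by row order in the data file. Identical data can then give different P values, and near the significance threshold they can give different conclusions. An infant without a partner drops out of the test even though the outcome was observed.

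**Working it through.** **The plan's own figure.** Sample Size gives 23 per group, "given α=.05 and a statistical power of 0.80 (β=.20"), from prevalences of 57% and 13%. A two-sided comparison of two independent proportions with continuity correction gives 22 per group. Two-sided Fisher exact power first exceeds 0.80 at 22 (0.826) and is 0.850 at 23. The stated size is therefore close to what an independent-groups comparison requires. The article does not name the test behind it, so this is consistent with independent groups but does not prove that they were assumed.

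**Inputs.** 55 per arm (Study Design, Sample Size); two-sided testing ("Two-tailed paired *t* tests"); α = .05. Normal data with equal SDs are assumed for illustration.

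**How P depends on the pairing.** Let the arms have equal sample SDs s, mean difference D and n per arm. Let r be the sample correlation that a chosen pairing happens to produce.

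- Independent test: t = D / (s√(2/n)), df = 2n − 2 = 108, critical value 1.982.
- Paired test: t = D / (s√(2(1 − r)/n)), df = n − 1 = 54, critical value 2.005.
- Hence t(paired) = t(independent) / √(1 − r).

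D, s and n are fixed by the data. Only r changes with the pairing. Under random pairing r has mean 0 and SD 1/√54 = 0.136, so its central 95% is about ±0.267.

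Take a data set with independent P = .050, so t = 1.982:

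- r = +0.267: t = 1.982/√0.733 = 2.315, P = .024.
- r = −0.267: t = 1.982/√1.267 = 1.761, P = .084.
- Paired P is below .05 when 1.982/√(1 − r) > 2.005, that is r > 0.0225, or 0.0225/0.136 = 0.17 SD above zero. The chance is about 43%.

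Simulation with 20,000 random pairings of one such data set agrees: central 95% of P from .025 to .083, full range .006 to .111, and 43% below .05.

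**Error rate and power under random pairing.** In 20,000 simulated null trials, type I error was .052 (paired) and .051 (independent). For an assumed difference of 0.50 SD, the noncentrality is 0.50 × √(55/2) = 2.62 for both tests. Power is .731 (paired, 54 df) and .738 (independent, 108 df).

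**Pairing that is not random.** If both arms are sorted by outcome in the same order before pairing, type I error is .74. If one arm is sorted in reverse, it is .007. These are extremes. They show how far the choice of pairing can move the result.

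**Infants lost.** The article states no attrition rate, so 15% in each arm is assumed. Expected observed infants: 55 × 0.85 = 46.75 per arm, 93.5 in total.

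- Pairs fixed before dropout: complete pairs 55 × 0.85² = 39.7. Loss (46.75 − 39.7)/46.75 = 15%.
- Pairs formed after dropout: only the excess of the larger arm is lost. The difference in arm sizes has SD √(2 × 55 × 0.85 × 0.15) = 3.75 and expected absolute value about 3.75 × 0.80 = 3.0 infants. Loss 3.0/93.5 = 3%.

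**The case against.** **It may be a slip, or refer to change over time.** The withdrawal scale and the parental symptom scales are measured at 2, 6 and 12 months, and paired tests suit within-infant change. But the sentence says the groups are what is compared, and it includes covariates, some of which are measured once. Comparison between times appears in the next sentence, under the analysis of covariance. If unpaired tests or within-infant tests were meant, the wording still needs correcting.

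**It is not shown to be the main test.** This stands. A reader might infer that the trial's main result will rest on an arbitrary pairing. The article labels no test primary, the analysis of covariance also covers the group comparison, and logistic regression is listed. It does not follow that the randomised comparison will go unreported.

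**The damage is modest if pairing is random.** This also stands. A reader might infer an inflated error rate or a real loss of power from halving the degrees of freedom. The figures show neither. Away from the threshold the conclusion may not move: at an independent P of .020 (a difference of about 0.45 SD with 55 per arm), the central 95% of paired P values is .008 to .040.

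**Matching could supply the pairs, or could itself discard randomised infants.** The article supports neither inference. Matching appears only among other techniques, with no variables, no stated use and no link to the t tests. It might serve the exploratory aim on hospitalisation and parental factors.

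**Conclusion.** The test is wrong as written: it requires pairs across the arms, and the design as described has none. The result is a P value that is undefined until someone chooses a pairing, cannot be reproduced without that choice and can be steered by it. At an independent P of .050 the random-pairing range is about .025 to .083, with about 43% of pairings significant. This rests on 55 per arm and normal data with equal SDs.

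The loss of observed infants is about 3% to 15%. It depends on an assumed 15% attrition and on whether partners are set after or before dropout; the higher figure should not be quoted alone.

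The point does not extend to a claim of systematic bias, or to a claim that the trial's only or principal between-group analysis is invalid.

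**What to change.** In Statistical Analysis, replace the paired t tests for the arm comparison with an independent-groups comparison:

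- a linear model for the Alarm Distress Baby Scale score, and logistic regression for a score of 5 or higher;
- all randomised infants with an outcome, analysed in the arm to which they were assigned;
- allowance for co-twins, who are eligible and allocated together, by cluster-robust standard errors or a random effect for family. A plain unpaired t test would wrongly treat co-twins as independent;
- adjustment for the randomisation strata (centre, single or twin pregnancy, Kangaroo Care at the public hospital).

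Reserve paired tests for within-infant change between visits and say so. State that matching will not be used for the randomised arm comparison.

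The cost is a change of wording in one section. Enrolment was complete and results were not yet published when the article was written, and no change to recruitment, visits or data collection is needed. The correction should be made and dated before the arms are compared.
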